#### 2.3.2 Usual care for people with MS

The standardized physical therapy comprises twelve 40-45-minute individualized face to face physiotherapy sessions, over a 6-week period, plus an individualized 30-minute daily home exercise program. The standardized program of physiotherapy exercises aims at improving trunk and pelvic stability, lower limb muscle length, strength, balance and control of movement, in accordance with the Bobath concept [46]. This exercise program is reflective of the general exercises typically undertaken within routine clinical practice in people with MS.

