### 2.4. Assessments/Procedure

#### 2.4.1 Experimental procedure

Potential participants learn of this study through personal contact, e-mails and printed advertisements posted at the two centers. The study team’s contact details are provided to enable interested participants to further enquire and participate in the study. Interested participants are provided with an information pack describing the study, supported by verbal information. They are screened for eligibility according to the pre-specified inclusion and exclusion criteria at the above-mentioned study sites. With inclusion criteria met, written informed consent of the participants are obtained. Group assignment is randomly performed where applicable by the principal investigators based on a generated list matched by age and gender. The randomization list is kept concealed (password protected, exclusively accessed by principal investigator) until intervention assignment. Only data analysts remain blinded to group allocation. Prior to the baseline measurement, participants undergo a physical examination (self-reported anamneses: verified diagnosis; current pain level, complaints and impairments; musculoskeletal/orthopedic examination) by a physician to rule out contraindications that restrict or prevent participation in regard to testing and exercise intervention. Baseline measurements (M1) are conducted three days before the first training session, comprising: (1) blood sampling, (2) self-reported questionnaires, (3) mobility, (4) balance and (5) strength testing. All participants, irrespective of group allocation, perform the test battery. Additional blood sampling is conducted immediately before and three days after the first training session in order to assess the acute reaction to the initial training bout. The follow-up measurement (M2) is conducted three days after the last training session. The follow up assessment session includes tests identical to those collected at baseline, with the addition of participant rating scores of the intervention program (5-point Likert-Scale regarding exercise selection, time effort and required equipment).

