Force capacity of the knee flexors and extensors are assessed via isokinetic dynamometry (University Outpatient Clinic—Potsdam: Con-Trex, MJ, Physiomed AG Germany; Sheba Medical Center–Tel Aviv: CSMi Computer Sports Medicine Inc., Stoughton, MA, USA) [54–56]. The isokinetic strength test of maximum voluntary contractions (MVC) is performed within a predefined range of motion of 70° (15° to 85° knee flexion) and at a motion velocity of 60°/s. Flexion and extension are performed in an alternating manner. The isokinetic protocol consists of a warm-up (10 repetitions; 50% of MVC, concentric) followed by five repetitions of concentric MVCs and a familiarization trial of five eccentric flexion/extension movements (50% MVC) followed by five repetitions of eccentric MVCs. Trials are separated by a one-minute break. For the evaluation of maximum force capacity, peak torque (Nm) and work (J) of concentric and eccentric knee flexion and extension will be considered.

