#### 2.4.3 Population-specific assessments

For LBP and CTRL, pain severity in regard to low back pain is assessed by the “Chronic Pain Grade questionnaire” considering the subscales of characteristic pain intensity, pain related disability and the overall pain grade classification [57, 58].

For PwMS and PwMS_STD_ the following questionnaires will be used in addition to the common assessments mentioned above: SF 36 quality of life in MS (SF-36), 12 item Multiple Sclerosis Walking Scale (MSWS-12), Modified Fatigue Impact Scale (MFIS), Falls Efficacy Scale International (FES-I). The MSWS-12 is currently the most widely, qualitative, patient-reported outcome measure assessing the patients’ perception of the impact of MS on walking ability. The MFIS is a modified form of the Fatigue Impact Scale based on items derived from interviews with MS patients concerning how fatigue impacts their lives. This instrument provides an assessment of the effects of fatigue in terms of physical, cognitive and psychosocial functioning. The SF-36 is one of the most widely used generic measures of health-related quality of life and has been shown to discriminate between subjects with different chronic conditions and between subjects with different severity levels of the same disease. This instrument addresses health concepts that are relevant to MS patients from the patient’s perspective. The SF-36 generates eight subscales and two summary scores. The eight subscales are: physical functioning, role limitations due to physical problems, bodily pain, general health perceptions, vitality, social functioning, role-limitations due to emotional problems, and mental health. The two summary scores are the physical component summary and the mental component summary. The FES-I is a self-administered questionnaire designed to assess fear of falling in different clinical populations. The questionnaire comprises 16 items, including a range of functional activities. Individuals are instructed to rate each activity on a 4-point Likert scale, depending on how concerned they are that they might fall if they did this activity, regardless of whether they actually perform it.

For LBP and CTRL force capacity is assessed additionally for the trunk flexors and extensors. The instrumentation as well as the protocol corresponds with the strength testing at the knee. Trunk motion is set to a range of 55° (45° flexion to 10° extension) [56].

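### The reference blood sample for the acute training response is drawn three days after a maximal eccentric strength test, so the acute contrast may be understated

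*Protocol article*

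**What the plan says.** All references are to the protocol article.

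- **Baseline visit (2.4.1).** "Baseline measurements (M1) are conducted three days before the first training session, comprising: (1) blood sampling, (2) self-reported questionnaires, (3) mobility, (4) balance and (5)". The fifth and last item is the strength test; blood is listed first. The same section adds: "All participants, irrespective of group allocation, perform the test battery".
- **Content of the strength test (2.4.2).** The knee protocol has a concentric part, then five eccentric familiarisation movements at half of maximum, "followed by five repetitions of eccentric MVCs".
- **Extra test in two groups (2.4.3).** "For LBP and CTRL force capacity is assessed additionally for the trunk flexors and extensors". The section states that the trunk protocol matches the knee protocol.
- **Acute-response samples (2.4.1).** "Additional blood sampling is conducted immediately before and three days after the first training session in order to assess the acute reaction".
- **Follow-up (2.4.1).** "The follow-up measurement (M2) is conducted three days after the last training session", with the baseline tests repeated, so blood is included.
- **Premise (Introduction).** The article accepts that eccentric load, above all when unaccustomed, may damage muscle, and that it is associated with an inflammatory response.
- **Analysis (2.6).** Muscle and inflammatory markers enter a repeated measures ANOVA with time and group as factors. The blood time points that form the time factor are not listed.

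**The concern.** The acute contrast needs a reference unaffected by recent eccentric exercise. The sample named for that purpose follows a maximal eccentric test by three days. That is also the delay at which the plan expects to see the effect of session 1. Any marker that is still raised three days after eccentric work may be raised in the reference too, and the subtraction would then remove part of the response it is meant to show.

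Because LBP and CTRL also perform the trunk test, the carry-over need not be equal across groups, and the group-by-time analysis could register that inequality as a difference in response to training. At stake is how the article's question on eccentric exercise and cytokines is answered, and the preliminary signal that section 2.5.2 hands to future studies. The feasibility outcomes are not affected.

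**Working it through.** The plan gives no figure to reproduce, so the check sets out the timeline and writes each contrast as a sum of parts.

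**Timeline (day 0 = first session, from 2.4.1)**

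| Sample | Day | Preceding load set by the plan |
|---|---|---|
| M1 blood | -3 | none, if drawn before the strength test |
| Pre-session | 0 | M1 test, 0 - (-3) = 3 days earlier |
| Post-session | +3 | session 1, 3 days earlier; M1 test, 3 - (-3) = 6 days earlier |
| M2 blood | last session + 3 | last session, 3 days earlier |

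**Notation.** S3 is the response to session 1 at three days. T3 and T6 are the responses to the M1 test at three and six days. Responses are assumed to add.

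**Contrasts**

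- Day +3 minus day 0 = (S3 + T6) - T3 = S3 - (T3 - T6)
- Day +3 minus M1 = S3 + T6
- Day 0 minus M1 = T3

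If the test response is non-negative and fades (T3 ≥ T6 ≥ 0), the first contrast is at or below S3 and the second at or above it. The two bracket S3, and the width of the bracket is (S3 + T6) - (S3 - T3 + T6) = T3, which the third contrast estimates.

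**Illustration with S3 = 1.** T3 and T6 are assumed values, because the article gives none.

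| T3 | T6 | Day +3 minus day 0 | Day +3 minus M1 |
|---|---|---|---|
| 0 | 0 | 1.00 | 1.00 |
| 0.10 | 0 | 0.90 | 1.00 |
| 0.10 | 0.05 | 0.95 | 1.05 |
| 0.25 | 0 | 0.75 | 1.00 |
| 0.50 | 0 | 0.50 | 1.00 |
| 0.50 | 0.25 | 0.75 | 1.25 |
| 0.50 | 0.50 | 1.00 | 1.50 |

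The stated contrast is unbiased if T3 = 0 or if T6 = T3. Otherwise, with a fading response, it is too small.

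**What the article says about load.** The knee test has 5 + 5 = 10 eccentric repetitions, five of them maximal. Section 2.3.1 gives 4 to 6 exercises, 2 to 3 sets and 10 to 15 repetitions: 4 × 2 × 10 = 80 up to 6 × 3 × 15 = 270 repetitions per session. Intensity differs between test and training, so the counts do not convert into T3/S3, but they leave room for a T3 near zero.

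**Groups.** The difference in bias between LBP/CTRL and the MS groups is (T3 - T6) in the former minus (T3 - T6) in the latter. The trunk test gives a reason for this to be non-zero. The article does not fix its size.

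**M2.** With C the lasting programme effect and L3 the residual of the last session at three days, M2 minus M1 = C + L3. For example, assumed values C = -0.5 and L3 = 0.5 give 0.

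**The case against.** The strongest reply is that the bias is unproven. The article gives no time course for any marker, the test is short, and T3 may be negligible. That stands as to size. It does not remove the timing problem: choosing a three-day draw to detect a response to eccentric load presumes that such a response can be present at three days.

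A second reply is that the M1 sample already exists and that the analysis section does not exclude it. This also stands, and it makes the remedy cheap. But 2.4.1 ties the acute reaction to the two additional draws and gives M1 blood no role in it.

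A reader might infer several stronger points that the documents do not support:

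- **That session 2 contaminates the day +3 sample.** Three sessions a week give a mean gap of 7/3 = 2.33 days, but a 3-2-2 day pattern leaves session 1 clear. A condensed article need not give the spacing. In the standard-care group, "plus an individualized 30-minute daily home exercise program" makes intervening exercise more likely, which is a reason to record it and does not show an error.
- **That M2 minus M1 fails its purpose.** Nowhere does the article say that this contrast must isolate lasting adaptation. If L3 is zero, it is clean.
- **That M2 should instead be compared with the post-session-1 sample.** The lags match, but this sets an accustomed bout against a first one, and the Introduction says damage is greatest when load is unaccustomed.
- **That a false finding of no reaction is most likely in MS.** The extra trunk load is in LBP and CTRL, so on that ground alone the added understatement would fall there.

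**Conclusion.** The point holds for the acute contrast. The reference sample is three days after a maximal eccentric test, the same lag used to read the session response, and day +3 minus day 0 equals S3 - (T3 - T6). It is understated if the test response is present at three days and has faded by six, possibly unequally between LBP/CTRL and the MS groups.

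The size is not derivable from the article and may be close to zero. No percentage should be attached to it, nor should all ten markers be assumed affected. The conclusion rests on additive responses and on a test response that does not grow after day three.

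For M2 minus M1 only a caution on interpretation is supported. Blood markers are secondary surrogate outcomes in a pilot of 12 per group, so this is a moderate point that deserves correction because the correction is cheap.

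**What to change.** 1. Confirm and state that M1 blood is drawn before strength testing.
2. Report day +3 minus M1 alongside day +3 minus day 0, by group. If the test response fades between days three and six, the two bracket the session response.
3. Report day 0 minus M1, by group, as the effect of the test battery.
4. Record whether any further session or prescribed home exercise preceded the day +3 draw.
5. State that M2 minus M1 blood changes include any residual response to the last session three days earlier.

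**Cost.** A few sentences of analysis text and one recorded item per participant. No extra samples are needed, and neither training nor the visit schedule changes.

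**Limits.** The M1-referenced contrast still contains any test response left at six days, so it should be reported beside the planned contrast and should not replace it. With 12 per group, day 0 minus M1 will be imprecise, and a small observed value would not prove that carry-over is absent.

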Regardless of the benefits, eccentric exercises may initially lead to muscle damage, impaired muscle function and delayed-onset muscle soreness, especially in unaccustomed loading situations. Therefore, it could be questioned whether the use of eccentric training in the therapy of clinical at-risk populations (e.g. elderly and frail people, people with diseases of the central nervous system, people with co-morbidities) is feasible [19]. Few studies have demonstrated that eccentric training is feasible and effective in cardiorespiratory disease [20], chronic obstructive pulmonary disease [21], after cancer therapy [22] and might also be relevant in obese patients [23]. Nevertheless, the transfer into the clinical practice is pending.

To date, the majority of eccentric training programs have been focused on orthopedic indications and prevention of muscular injuries [24, 25]. Considering eccentric muscle contractions result in decelerating movements that counteract gravity [26], eccentric training could also prepare the body, and especially the trunk, for high loads that may occur repeatedly and unexpectedly during daily and work-related activities. Therefore, it is potentially beneficial in the prevention and treatment of low back pain; one of the most common clinical conditions worldwide [27]. Generally, exercise can reduce the intensity of low back pain as well as pain-dependent limitation, improve function, and prevent recurrence [28, 29]. Although there is currently no evidence indicating a preferable mode, common recommendations emphasize that exercise programs should include elements to increase muscle strength and neuromuscular control, as these factors contribute significantly to maintaining trunk stability [30, 31]. Further, the ability of the neuromuscular system to adequately compensate for load-induced dysfunction and maintaining spinal stability is highly relevant in the prevention of low back pain and its patho-anatomical consequences. Surprisingly, despite its high potential to improve muscle strength and neuromuscular capacity, eccentric training has not been thoroughly investigated as a treatment of low back pain.

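### The pre-session-1 blood sample follows the maximal eccentric strength tests by three days, so it may not be a resting reference for the acute reaction to training

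*Protocol article*

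**What the plan says.** Section 2.4.1 sets the timing: "Baseline measurements (M1) are conducted three days before the first training session". The M1 components are listed as "1) blood sampling, (2) self-reported questionnaires, (3) mobility, (4) balance and (5) strength testing", so blood comes first in the list and strength testing last. The same section adds: "All participants, irrespective of group allocation, perform the test battery".

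Section 2.4.2 describes the knee test. After a concentric part and an eccentric familiarization at half effort, it is "followed by five repetitions of eccentric MVCs". Section 2.4.3 adds: "For LBP and CTRL force capacity is assessed additionally for the trunk flexors and extensors", with a protocol matching that for the knee.

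For the acute blood response, Section 2.4.1 says: "Additional blood sampling is conducted immediately before and three days after the first training session", and gives the purpose as "in order to assess the acute reaction to the initial training bout". It states no washout after the strength tests and no correction for them. Section 2.6 plans a two-way repeated measures ANOVA (time by group) for the blood markers and names no reference sample.

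**The concern.** A pre/post pair measures the reaction to a bout only if the pre-value is a resting value. Here it is drawn three days after maximal eccentric work. By sampling at day +3, the protocol treats three days as a lag at which a reaction to eccentric loading is worth measuring. It does not explain why a sample three days after the tests can be taken as free of one. The protocol's own Introduction says that "eccentric exercises may initially lead to muscle damage, impaired muscle function and delayed-onset muscle soreness, especially in unaccustomed loading situations".

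There are two separate consequences.

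- **Carry-over.** Any test reaction in the pre-session sample enters the session-1 contrast. The amount may differ between LBP/CTRL, who also do the trunk tests, and the two MS groups, who do not. Such a difference would enter the group-by-time interaction.
- **Prior exposure.** Within the study, session 1 is not the first unaccustomed eccentric load. This holds even if the markers have returned to rest by session 1.

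At stake is the reading of the creatine kinase, myoglobin and inflammatory-marker response. The Introduction calls the cytokine response to eccentric training in MS an open question, and the Discussion says the study will inform on inflammatory reactions.

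**Working it through.** **Timeline** (session 1 = day 0; Section 2.4.1). Strength tests: day −3. Pre-session sample: day 0. Post sample: day +3.

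- Tests to pre-session sample: 0 − (−3) = 3 days
- Session 1 to post sample: 3 − 0 = 3 days
- Tests to post sample: 3 − (−3) = 6 days

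**Eccentric load in the tests** (Sections 2.4.2 and 2.4.3). Five maximal repetitions in each of two directions give 5 × 2 = 10 maximal eccentric contractions per knee, and 10 more at the trunk in LBP and CTRL. The text does not say whether one or both legs are tested, so the total is 10 or 20 in the MS groups and 20 or 30 in LBP and CTRL.

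**Load in session 1** (Section 2.3.1). From 4 × 2 × 10 = 80 to 6 × 3 × 15 = 270 repetitions. By count, the tests are 10/270 = 3.7% to 10/80 = 12.5% of a session for 10 contractions, 7.4% to 25% for 20, and 11.1% to 37.5% for 30. The test contractions are maximal and the training repetitions need not be, so these ratios compare dose counts and do not estimate relative effect.

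**Carry-over identity.** Let B be the resting level, T the session-1 reaction at three days, and R3 and R6 the test reaction three and six days after M1. Assume that effects add and that M1 blood is drawn before the strength tests.

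- M1 = B
- Pre-session = B + R3
- Post = B + R6 + T

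The three contrasts are:

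- Pre-session − M1 = R3
- Post − pre-session = T + R6 − R3
- Post − M1 = T + R6

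**Illustration with T = 1.** R3 and R6 are assumed, because the documents give neither. Each cell shows post − pre-session, then post − M1.

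| R3 | R6 = 0 | R6 = 0.5 × R3 | R6 = R3 | R6 = 1.5 × R3 |
|---|---|---|---|---|
| 0 | 1.00; 1.00 | 1.00; 1.00 | 1.00; 1.00 | 1.00; 1.00 |
| 0.05 | 0.95; 1.00 | 0.975; 1.025 | 1.00; 1.05 | 1.025; 1.075 |
| 0.10 | 0.90; 1.00 | 0.95; 1.05 | 1.00; 1.10 | 1.05; 1.15 |
| 0.25 | 0.75; 1.00 | 0.875; 1.125 | 1.00; 1.25 | 1.125; 1.375 |
| 0.50 | 0.50; 1.00 | 0.75; 1.25 | 1.00; 1.50 | 1.25; 1.75 |

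The stated pair understates T when R6 < R3, is unbiased when R6 = R3, and overstates T when R6 > R3. M1 as sole reference is exact only when R6 = 0.

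The two contrasts that end at day +3 differ by (T + R6) − (T + R6 − R3) = R3, which the first contrast measures. If 0 ≤ R6 ≤ R3, post − pre-session lies at or below T and post − M1 at or above it, so together they bracket T. If the reaction is still rising (R6 > R3), both overstate T.

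**The case against.** Five points can be made against the concern.

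1. **No evidence of carry-over.** The documents give no size or time course for any marker after the tests, and the Introduction says only that eccentric loading may cause damage. This stands. A reader might infer that the pre-session sample does carry a reaction and that the session-1 response is understated. The documents support neither as fact, and the direction depends on R6 against R3.
2. **The scheme already holds most of the remedy.** M1 has its own blood draw, listed before strength testing, and nothing bars its use. Choosing contrasts is commonly left to an analysis plan. This stands in part. Section 2.4.1, however, already ties the acute reaction to the day 0 and day +3 samples, and following that text literally can give a biased answer.
3. **M1 as sole reference has its own flaw.** It leaves R6 in the contrast. This stands, and is why all three contrasts are needed.
4. **The consequence is limited.** Table 1 lists blood markers as surrogate outcomes; its safety entries are adverse events, pain and soreness. The feasibility criterion in Section 2.6 uses only attendance and completion of M2. If group D is sampled on the same days, the shared knee-test reaction cancels in the comparison of the two MS groups. LBP and CTRL have no untrained comparator. Their comparison with the MS groups also differs by country, population and dynamometer, so the trunk tests are only one of several differences there. All of this stands.
5. **Soreness.** A reader might infer that the session-1 soreness score is contaminated by the tests too. Section 2.3.1 does not say whether soreness is scored before or after the exercises, so no such claim is made.

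**Conclusion.** The point holds in a limited form. The schedule is unambiguous: the reference sample for the acute reaction comes three days after maximal eccentric testing, with no washout or correction stated. It may not be a resting value, and session 1 is not the first eccentric load in the study.

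The size and direction of any bias are unknown. If the test reaction is gone by day +3 and its day 0 level is 5% to 50% of the session-1 reaction, the stated pair understates that reaction by 5% to 50%. With no test reaction, or a constant one, there is no bias. With one still rising at 1.5 times its day 0 level, the same range gives an overstatement of 2.5% to 25%. These figures rest on additive effects and assumed values.

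The issue touches a secondary, exploratory outcome in a pilot of 12 per group. It alters neither the feasibility decision nor any safety item in Table 1. It should still be corrected, because a small acute marker response could be read as reassurance and the correction uses samples already planned.

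**What to change.** In Section 2.4.1, state that M1 blood is drawn before strength testing. The listed order suggests this but does not fix it.

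In Sections 2.4.1 and 2.6, report three contrasts for each blood marker, by group:

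- M1 to pre-session 1: the three-day reaction to the strength tests.
- Pre-session 1 to +3 days: the additional change after session 1.
- M1 to +3 days: the combined change from rest, described as including any test reaction left six days after testing.

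State that the second contrast alone is not the full acute reaction to a first eccentric bout, and that LBP and CTRL had trunk testing beforehand while the MS groups did not.

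Placing the strength tests further ahead of session 1, with the same gap in every group, is optional. It could reduce carry-over, but the documents give no basis for choosing a gap, and the tests would still precede session 1 as an eccentric load.

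The cost is a little more analysis and a more cautious interpretation. No extra samples or visits are needed unless the strength tests are moved, which would mean a longer lead-in or a split M1 visit.
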